### Quality and safety

Centers are allowed to participate in the DIPLOMA trial if they perform at least 15 distal pancreatectomies (any diagnosis) annually. Surgeons are allowed to participate if they have performed over 50 pancreatic resections (minimally invasive or open for any diagnosis), 50 advanced minimally invasive gastrointestinal resections (defined as any procedure beyond diagnostic laparoscopy, cholecystectomy, appendectomy, and inguinal hernia repairs), and 20 MIDPs for any diagnosis, including 5 for PDAC, and 10 ODPs for PDAC in the last 5 years. Surgeons that only perform open procedures in the trial should have performed over 50 pancreatic resections (for any diagnosis), 20 ODPs for any diagnosis, and 10 ODPs for PDAC in the last 5 years. All MIDP surgeons will be asked to send a recorded and anonymized video of a MIDP performed before the start of the trial. This video will be shortened and evaluated by an independent expert who is blinded for the surgeon and the clinical outcome. The videos are scored in five domains of technical skill (gentleness, tissue exposure, instrument handling, time and motion, and flow of the operation) using the methods described by Birkmeyer et al. [39]. Each domain will be rated on a scale of 1 to 5, where 1 indicates the skill expected of a general surgical resident and 5 the skill of a master minimally invasive pancreatic surgeon. A score of 3 points for every domain is considered an average minimally invasive pancreatic surgeon and should be scored in order to participate in the DIPLOMA trial. In addition, during operations (MIDP and ODP) within the DIPLOMA trial, surgeons will be asked to take photos of the pancreatic transection margin and the pancreatic bed (posterior margin) and send these to the trial coordinator, to objectify surgical quality.

All adverse events will be recorded up to 90 days postoperatively. Serious adverse events will be reported through a web portal (www.toetsingonline.nl) to the Dutch central committee on research involving human subjects (in Dutch: centrale commissie mensgebonden onderzoek) and the institutional review board (Medical Ethics Committee of Amsterdam UMC, location Academic Medical Center). Serious adverse events that have to be reported to the study coordinator within 24 h are unplanned intensive care unit admission; any surgical, endoscopic, or interventional radiology intervention (excluding feeding tube placement); readmission; and mortality (regardless of cause). The remaining adverse events are recorded in a yearly overview list. An independent data safety monitoring board (DSMB) is appointed to evaluate the study safety parameters. When each 50th included patient has completed 30 days of follow-up, the DSMB will meet in order to assess the safety parameters. This meeting may be either a telephone or video conference. The DSMB exists of two independent statisticians, one independent gastroenterologist, and two independent surgeons. One of the clinicians is appointed as the DSMB chairman and a second member as secretary. The minutes of these meetings will be sent to the institutional review board of the study by the study coordinator and the trial steering committee. The DSMB will not be blinded and will be fully informed on all SAEs. The DSMB can request a full report of specific study outcomes whenever required. The study coordinator and principal investigator will only be present during the start (open discussion) of the DSMB meeting to provide the data and provide background information.

### Ethics

The DIPLOMA trial will be conducted according to the principles of the Declaration of Helsinki (64th version, October 2013) and in accordance with the local laws and regulations, such as in the Netherlands the Medical Research Involving Human Subjects Act. The local principal investigator is responsible to adhere to local laws and regulations. The independent ethics review board of the Amsterdam UMC, location Academic Medical Center (Amsterdam, the Netherlands), and University Hospital Southampton NHS Foundation Trust (Southampton, UK) have both approved the study protocol. Furthermore, approval from all local ethics committees of participating centers was also obtained. The trial is registered in the ISRCTN registry: ISRCTN44897265.

### Statistical aspects

#### Sample size calculation

The DIPLOMA trial is designed as a non-inferiority trial, hypothesizing that in patients with pancreatic cancer the rate of microscopically radical (R0) resection rate of MIDP is non-inferior to ODP. Based on data collected for the retrospective DIPLOMA cohort study (1377 patients, matched based on propensity scores) [18], the sample size is calculated with the following assumptions: 5% one-sided significance level (*α*), 80% power (1-*β*), expected R0 rate in the open group of 58%, expected R0 resection rate in the minimally invasive group of 67%, and a non-inferiority margin of 7%. Based on these assumptions, a sample size of 226 patients (113 patients per arm) is required. Including 2.5% drop-out after randomization (patients who undergo no surgery after randomization) and 10% metastasized disease leads to a total number of patients to be randomized of 258 (129 per study arm).

#### Statistical analysis

Primary and secondary endpoints will be crosschecked with data from primary sources, and a blinded adjudication committee will check them against the used definitions. The primary endpoint (R0 resection rate) will be tested for non-inferiority using the chi-square test as described by Dunnett and Gent [40]. The distribution of variables will be determined using several plots (boxplot, Q-Q plot, and histogram) and the Kolmogorov-Smirnov, Shapiro-Wilk, and Levene’s tests as appropriate. For comparison of normally distributed continuous variables, the independent samples *t*-test will be used and values will be expressed as means with standard deviations. Continuous non-normally distributed variables will be compared using the Mann-Whitney *U* test and values will be expressed as medians with interquartile ranges. Categorical variables will be compared by chi-square or Fisher’s exact test as appropriate, and values will be expressed as proportions. A two-tailed *p*-value < 0.05 will be considered statistically significant. Where possible, risk ratios with 95% confidence intervals will be reported. For the primary study outcome, the lower limit of the two-sided 90% confidence interval of the difference in proportions will be reported and compared with the non-inferiority margin. Time to event endpoints, such as time to functional recovery, time to recurrence, and overall survival, will be calculated using Kaplan-Meier estimations. A Cox regression analysis will be performed to investigate predictors of postoperative survival. All parameters with a *p*-value < 0.1 in a univariable analysis are included in the multivariable Cox regression analysis. Multivariable logistic regression analyses are performed to determine predictors for primary and secondary study outcomes, for example, R0 resection, the occurrence of major complications, and postoperative pancreatic fistula. Predictors for receiving adjuvant chemotherapy will be assessed and additional “as treated” analysis will be performed. Subgroup analysis will be performed comparing outcomes for patients with and without neoadjuvant chemotherapy. Intra-operative details and primary endpoint of this study are expected to be complete. For patients who are lost to follow-up, a sensitivity analysis will be performed to determine best case and worst case scenarios. A detailed statistical analysis plan will be drafted prior to database lock. Despite all prior preventive measures taken, a complex international trial may evoke unforeseen situations after database lock that threaten data integrity and can only be resolved by unlocking the database prior to the final analysis. For purpose of transparency and reproducibility, the statistical analysis plan will therefore also describe the procedure to be followed when such situations arise.

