### Randomization

Patient recruitment and the collection of written informed consent are performed at the outpatient clinic. Allocation of patients to MIDP or ODP is performed centrally by the study coordinators using a concealed online computer-controlled permuted-block randomization module (Castor EDC, CIWIT B.V., Amsterdam, the Netherlands). Randomization between MIDP and ODP will be performed in a 1:1 ratio. The block sizes will be subject to random variation with block sizes varying between 4, 6, and 8 patients. The entire randomization will be concealed to all involved investigators. Randomization will be stratified for annual distal pancreatectomy volume (< 20, 20–40, and > 40) of participating centers. In addition, randomization will be stratified for tumor involvement beyond the pancreas and spleen to correct for differences in extended resections (adrenal gland involvement is defined as extended resection according to the ISGPS guideline) [23]. Randomization will take place as soon as distal pancreatectomy is planned (i.e., date of surgery is available) in order to reduce the drop-out rate after randomization. Only patients that do not receive surgery are considered a drop-out and will not be analyzed. All other randomized patients (including patients with peroperative diagnosed metastasized disease) will be analyzed according to the intention-to-treat principle. Patients will be coded by a numeric randomization code and the study coordinator will be the only one with access to it. The source data will be stored digitally and will be kept by the project leader for 15 years after the last patient’s follow-up is completed.

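### The primary non-inferiority test and 90% interval do not use the two randomization strata: still valid, but conservative if the strata predict R0, with roughly 0 to 4 points of power forgone

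*Protocol article*

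**What the plan says.** **Allocation.** The Randomization section uses 1:1 permuted blocks of 4, 6 or 8. It states that "Randomization will be stratified for annual distal pancreatectomy volume", with classes below 20, 20 to 40 and above 40 per year. It adds that "randomization will be stratified for tumor involvement beyond the pancreas and spleen to correct for differences in extended resections". Crossed, the two factors give six strata.

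**Analysis.** Under Statistical analysis, the R0 rate "will be tested for non-inferiority using the chi-square test as described by Dunnett and Gent". The decision compares the lower bound of a two-sided 90% interval for the difference in R0 proportions with the margin. Neither the test nor the interval is described as stratified or adjusted. Multivariable logistic regression for R0 is planned, but to find predictors, and neither stratification factor is named there. A detailed statistical analysis plan is announced for before database lock; it is not at hand.

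**Planning figures.** Sample size calculation gives a "5% one-sided significance level", 80% power, R0 rates of 58% (open) and 67% (minimally invasive), "a non-inferiority margin of 7" points, and concludes that "a sample size of 226 patients (113 patients per arm) is required".

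**The concern.** Blocking within strata balances the arms on the stratum factors. If those factors predict R0, that balance removes between-stratum variation from the true sampling error of the difference. The crude 2x2 standard error still counts that variation, so it overstates the uncertainty. The interval is then wider than it needs to be, and the test rejects less often than its nominal level allows.

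The protocol article names a specific unstratified test and builds its decision rule on an unadjusted difference. This is therefore a stated choice that an analysis plan following the article would carry forward, rather than a detail left open. At stake is efficiency: precision that the design has already bought through stratification is not collected in the analysis.

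**Working it through.** **1. The plan's own figure.** Inputs are from Sample size calculation: open rate 0.58, minimally invasive rate 0.67, margin 0.07, one-sided 5%, 80% power.

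n per arm = (0.58×0.42 + 0.67×0.33) × (1.645 + 0.842)² / (0.09 + 0.07)² = 0.4647 × 6.183 / 0.0256 = 112.2, so 113 per arm and 226 in total.

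With the Dunnett-Gent null variance the result is 112.5, again 113. The stated figure reproduces for the unadjusted test. Power at 113 per arm: SE = √(0.4647/113) = 0.0641; 0.16/0.0641 − 1.645 = 0.850; Φ(0.850) = 80.2%.

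**2. What stratified blocking does to the variance.** Let B be the between-stratum variance of the R0 rate, with the same risk difference in every stratum. The crude variance is V/n, with V = p₁(1−p₁) + p₂(1−p₂). The true variance under stratified blocks is about (V − 2B)/n. Hence:

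- error rate of the crude test = Φ(−1.645 × √[V/(V − 2B)])
- power of the crude test = Φ([0.16 − 1.645·SE_crude] / SE_true)
- power of the stratified test = Φ(0.16/SE_true − 1.645)

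**3. Worked case (assumed stratum effects).** The documents give no stratum sizes and no R0 rates by stratum. Assume volume shares of 30/40/30%, 30% extended disease, an overall open rate of 58%, and logit effects of 0.5 per volume step and 1.5 for extension. Open-arm R0 rates then run from 23% to 79% across strata and B = 0.0322, or 13% of 0.58×0.42.

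- At the margin (58% vs 51%): V = 0.4935; √(0.4935/0.4292) = 1.072; error rate Φ(−1.764) = 3.9%.
- At 58% vs 67%: SE_true = √((0.4647 − 0.0643)/113) = 0.0595. Crude power = Φ((0.16 − 0.1055)/0.0595) = 82.0%. Stratified power = Φ(0.16/0.0595 − 1.645) = 85.2%.
- Interval half-width: 10.5 points crude, against 1.645 × 0.0595 = 9.8 points.

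**4. Simulation.** Setup: 15,000 trials per scenario, N = 226, six strata, blocks of 4/6/8. The crude test is Dunnett-Gent; the stratified analysis is a Mantel-Haenszel risk difference with Sato variance. Simulation error on the error rate is about 0.2 points. Ranges cover 15% and 30% extended disease.

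| Assumed strata (logit per volume step; extension) | Error rate, crude | Error rate, stratified | Power, crude | Power, stratified |
|---|---|---|---|---|
| Not prognostic (0; 0) | 5.1% | 5.2% | 80.3% | 80.2% |
| Weak (0.25; 0.75) | 4.5–4.7% | 4.8–5.0% | 80.6–80.9% | 81.3–81.7% |
| Moderate to strong (0.5; 1.5) | 3.8–4.1% | 5.0–5.1% | 81.5–81.6% | 83.8–85.3% |
| Very strong (0.75; 2.25) | 3.0–3.5% | 5.0–5.3% | 82.0–83.7% | 86.3–89.7% |

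The unadjusted 90% interval gives the same error rates as the crude test to within 0.1 point.

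A second simulation (12,000 runs) set the stratum effects in percentage points and used a stratified score test. It agrees:

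- 30% extended with R0 25 points lower, and 8 points per volume class: crude 4.2% error and 80.9% power; stratified 4.9% and 82.6%.
- 35% extended with R0 35 points lower, and 10 points per class: crude 3.7% and 82.2%; stratified 5.1% and 85.2%.
- 20% extended with R0 10 points lower: 80.0% against 80.1% power, no material difference.

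**The case against.** Several points on the other side are sound.

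- **Validity.** A reader might infer that the error rate is wrong in a way that undermines a positive result. It is not. The crude rate departs from 5% only if the strata are prognostic, and then downward; 5% stands as an upper limit.
- **Planned power.** A reader might infer that the trial is underpowered. The 226 was sized for the unadjusted comparison, reproduces, and gives at least 80% in every scenario. What is forgone is a gain on top of the target.
- **Size.** The stratum effects are assumed, and the design narrows them. Involvement or abutment of major vessels is excluded, the tumor must be judged radically resectable by both routes, and only the transection and posterior margins count for R0. Centres need at least 15 distal pancreatectomies a year, so the lowest volume class is 15 to 19. With 15% extended disease, R0 15 points lower there and no volume effect, B = 0.15×0.85×0.15² = 0.0029, about 1.2% of 0.2436, and the error rate is about 4.9%.
- **Contradiction.** The stated purpose of stratifying on extension can be read as balance by design. It does not promise an adjusted analysis, so the two sections do not conflict.
- **Equal R0 rates.** Power would be only 28% if both rates were 58%: 0.07/√(2×0.58×0.42/113) = 1.066; Φ(1.066 − 1.645) = 0.281. That follows from planning on a 9-point advantage; it is a separate matter that stratifying would barely change.

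Two further objections carry less weight. Handling of strata is often left to the analysis plan, but here the article fixes an unstratified test. By submission 217 of 258 patients had been randomized, but the analysis plan was still to be drafted before database lock, so the choice could still be made without knowledge of results.

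**Conclusion.** The point holds as one of efficiency. The primary test and interval ignore the factors used to randomize. If those factors predict R0, the analysis is conservative: an error rate of about 3.8% to 4.7% for weak to moderately strong strata, an interval half-width up to about 0.8 point too wide on 10.5, and about 1 to 4 points of power given up. If they do not predict R0, the loss is nil. Larger losses (4 to 6 points) appear only under very strong effects, which the eligibility rules make hard to credit.

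The mechanism is certain; the size is not, because it rests on assumed stratum shares and R0 rates and on a constant risk difference. The documents do not support reading this as an invalid test, a shortfall against the planned 80%, or a contradiction between sections.

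**What to change.** In the analysis plan, before database lock and before anyone drafting it has seen R0 results by arm:

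- Make the primary estimate a risk difference stratified by the two randomization factors, for example Mantel-Haenszel weights with score (Miettinen-Nurminen) or Sato-variance limits.
- Declare non-inferiority if the lower limit of its two-sided 90% interval lies above -7%.
- Prespecify how sparse strata are pooled, for example by collapsing volume classes within the extended-disease stratum. With 15% extended disease and 30% of patients in a volume class (assumed shares), a cell would hold about 226 × 0.15 × 0.30 = 10 patients over both arms.
- Keep the unstratified Dunnett-Gent test as a supportive analysis.

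The margin keeps its meaning: with near 1:1 allocation in each stratum, the Mantel-Haenszel weights are close to proportional to stratum size, so the target remains the overall difference in R0 rates.

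Cost: analysis-plan wording, a documented change of the named primary test, and standard software. Both factors are already recorded at randomization. No more patients are needed, and with non-prognostic strata the power is essentially unchanged (80.2% against 80.3%).

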Based on these results, the European Consortium on Minimally Invasive Pancreatic Surgery (E-MIPS) initiated the DIPLOMA study (distal pancreatectomy, minimally invasive or open, for malignancy). First, an international retrospective cohort study was performed including 1377 patients who underwent distal pancreatectomy (minimally invasive or open) for PDAC between 2007 and 2015 [18]. Patients after MIDP and ODP were matched using propensity scores in order to correct for standard demographics and known confounders. This study showed higher R0 resection rates for MIDP (67% versus 58%, *p* = 0.02), but lower median number of harvested lymph nodes [14 (interquartile range (IQR) 8–22) versus 22 (IQR 14–31), *p* < 0.001] with similar survival [29 (95% CI 23–35) versus 31 (95% CI 24–38) months for MIDP and ODP, respectively, *p* = 0.98] [18]. However, MIDP was associated with lower rates of lymphovascular tumor invasion, perineural tumor invasion, and lower lymph node stage insinuating that, despite matching, treatment allocation bias could still have influenced these results. Several other multicenter matched cohort studies on MIDP versus ODP for PDAC showed comparable outcomes, thus supporting the prevailing oncological uncertainty [19, 20].

The objective of the DIPLOMA trial is to compare the microscopically radical (R0) resection rate, survival, complications, quality of life, and costs after MIDP and ODP in patients with suspected or proven PDAC of the pancreatic body or tail. The outcome of the DIPLOMA trial will guide the further implementation of MIDP worldwide.

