### Secondary outcomes

The most important secondary outcomes are overall survival, time and site of disease recurrence, and postoperative time to functional recovery. Other secondary outcomes of this trial include intra-operative parameters (type of surgery (laparoscopic or robot-assisted), conversion, method of pancreatic transection, vessel resection, operative time, blood loss, and blood transfusion) and postoperative outcomes (major complications, delayed gastric emptying, pancreatic fistula, post-pancreatectomy hemorrhage, surgical site infection, serum levels of CA 19.9 and CEA, postoperative intervention, intensive care unit admission, organ failure, length of hospital stay, readmission, (time to) start of adjuvant therapy). Additional to the primary outcome, other pathology outcomes are recorded, such as tumor size, specimen length and weight, histology grading, distance from the tumor to all margins, number of retrieved lymph nodes, number of positive lymph nodes, lymphovascular and perineural tumor invasion, and venous and arterial tumor involvement. For the economical evaluation, costs (intra-operative and postoperative costs) and quality of life are assessed.

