### Data collection and patient follow-up

The required clinical data will be collected after randomization, i.e., from hospitalization up to 36 months postoperatively using standardized (online) case report forms (Castor EDC, CIWIT B.V., Amsterdam, the Netherlands) by the local treating physicians. All data is stored in an electronic database (Castor EDC, CIWIT B.V., Amsterdam, the Netherlands). Data monitoring is performed by the study coordinators who will crosscheck the case report forms with source data. Baseline characteristics (age, sex, performance status (Karnofsky score)), ASA physical status, body mass index, previous abdominal surgery, diabetes mellitus, preoperative imaging conclusion including tumor size and involvement of other organs and vessels, neoadjuvant treatment, serum levels of Hba1C, CA 19.9 and CEA, and baseline quality of life measures will be recorded before randomization. For all patients, the most recent preoperative imaging will be sent anonymously to the study coordinator. This will follow local ethical and privacy rules in every center. After completion of the study, all imaging modalities will be reassessed by two expert radiologists independently in order to define the preoperative pancreatic cancer stages. In case of disagreement between the expert radiologists, a third expert radiologist will be invited and discussion will take place until consensus is reached. The required clinical data will be collected after randomization, i.e., from hospitalization up to 36 months postoperatively using standardized (online) case report forms by the local treating physicians, and will be crosschecked with source data by the study coordinators. For quality of life, the EQ-5D-5L, QLQ-C30, and PAN-26 questionnaires are used. These will be sent to the participating patients at baseline, 14, 30, 90, and 180 days after surgery. Patients will also receive a questionnaire at 90 days and 365 days after surgery which focuses on readmissions, complications, body image, and adjuvant therapy. Patients will be followed up at the outpatient clinic every 6 months during the first 2 years after surgery and after 36 months after surgery (i.e., at 6, 12, 18, 24, 36 months). During these follow-up moments, patients will undergo an abdominal CT scan and serum levels of CA 19.9 and CEA tumor markers will be assessed.

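### The blanket unadjusted t-test or Mann-Whitney rule, applied to quality of life, ignores the baseline score and the correlation between visits and so loses precision

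*Protocol article*

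**What the plan says.** The stated objective (Background) includes comparing "survival, complications, quality of life, and costs after MIDP and ODP". Data collection and patient follow-up gives the instruments: "For quality of life, the EQ-5D-5L, QLQ-C30, and PAN-26 questionnaires are used". It gives the schedule: "These will be sent to the participating patients at baseline, 14, 30, 90, and 180 days after surgery". It also says that "baseline quality of life measures will be recorded before randomization", so the baseline score cannot be influenced by allocation and is a valid covariate.

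The Statistical analysis section sets a general rule for continuous variables. If they are normally distributed: "For comparison of normally distributed continuous variables, the independent samples" t-test. If they are not: "Continuous non-normally distributed variables will be compared using the Mann-Whitney" U test. Separate methods are given for the primary endpoint (a non-inferiority chi-square test) and for time-to-event endpoints (Kaplan-Meier). The regression models named are Cox for survival and logistic, the latter with binary outcomes as examples. Both serve to find predictors. No model is named for a continuous outcome or for repeated measurements. The section does not mention quality of life by name, and it says that an SAP will follow before the database is locked.

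**The concern.** A two-sample test of the scores at a given visit uses neither the patient's own baseline score nor the scores at the other visits. In quality-of-life data the baseline is usually among the best predictors of later scores. Leaving it out makes the confidence interval wider than it need be and leaves any chance baseline imbalance in the estimate. Using one visit at a time also gives up what correlated visits say about a patient who missed one questionnaire.

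The trial has taken trouble over these data. It uses three instruments and five time points, and Trial status records that the 14-day quality-of-life questionnaire was added by amendment. At stake is how sharply the trial can answer a question that its objective names.

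**Working it through.** **The plan's own figure.** The only sample size in the article is for R0. With 58% and 67%, a margin of 7%, one-sided alpha of 5% and 80% power, the distance from the margin is 0.67 − 0.58 + 0.07 = 0.16. Then n = (0.58×0.42 + 0.67×0.33) × (1.645 + 0.842)² / 0.16² = 112.2, so 113 per arm and 226 in total. Inflation gives 226 / (0.975 × 0.90) = 257.5, so 258. The stated figures reproduce and this point does not touch them. They serve below only as a convenient size of arm.

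**Inputs.**
- Follow-up visits: 4, plus a pre-randomization baseline (Data collection and patient follow-up).
- Two-sided 5% level for comparisons other than the primary (Statistical analysis).
- Patients per arm: 113 (Sample size calculation). The number returning questionnaires may differ. The variance ratios do not depend on it.
- Correlation r between baseline and follow-up: **not in the documents**. It is assumed to be 0.3 to 0.7 and, for the four-visit average, equal between all pairs of visits. No standard deviation is given either, so differences are in SD units.

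**Formulas.** The large-sample variance of the arm difference is taken relative to an unadjusted t-test at one visit (= 1):
- one visit, adjusted for baseline: 1 − r²
- one visit, change from baseline: 2(1 − r)
- mean of four visits, adjusted for baseline: (1 + 3r)/4 − r²
- equivalent patients per arm at one visit: 113 / (1 − r²)
- detectable difference at 80% power: (1.960 + 0.842) × √(2v/113), where v is the relative variance. For v = 1 this is 0.373 SD.

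| r (assumed) | Baseline-adjusted, one visit | 113 per arm acts like | Detectable difference (SD) | Power at 0.373 SD | Change score | Four-visit mean, baseline-adjusted |
|---|---|---|---|---|---|---|
| 0.3 | 0.91 | 124 | 0.356 | 84% | 1.40 | 0.385 |
| 0.5 | 0.75 | 151 | 0.323 | 90% | 1.00 | 0.375 |
| 0.7 | 0.51 | 222 | 0.266 | 97.5% | 0.60 | 0.285 |

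At one visit, adjustment therefore cuts the variance by 9%, 25% or 49%. For the average over four visits, baseline adjustment together with all visits cuts it by about 61% to 72%. That is a different quantity from the effect at a single visit.

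**Change scores.** The article neither states nor excludes a t-test on change from baseline. It would use the baseline, but for r below 0.5 its variance is larger than that of the unadjusted test. It is also above the adjusted variance at every r in the table.

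**Multiplicity.** Four tests per scale at 5% would give 1 − 0.95⁴ = 18.5% if they were independent, and less when they are correlated. Four visit-wise contrasts from a single model face the same problem. Only naming a principal scale and time point reduces it.

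**The case against.** The strongest reply is that the article never says how quality of life will be tested. The rule is generic and is ordinary for single measurements such as blood loss or operative time. The longitudinal model for a secondary patient-reported outcome is normal SAP content, and an SAP is announced. Part of this stands: the rule reaches quality of life only through general wording, and the SAP may replace it. But the section gives separate methods for the primary and time-to-event endpoints and none for repeated scores. What remains is therefore a stated rule that suits these data poorly, not just a detail left open.

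It is also fair to say that the gain rests on an assumed correlation. At 0.3 it is modest, and correlation with baseline may be lower at day 14, soon after major surgery. Quality of life is also not among the outcomes that Secondary outcomes ranks as most important. It appears there with the economic evaluation: "For the economical evaluation, costs (intra-operative and postoperative costs) and quality of life are assessed".

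A reader might infer three stronger things that the documents do not support:
- *That the comparison is biased.* Under randomization the unadjusted comparison is unbiased in complete data.
- *That patients who die or stop returning forms drop out of sight.* The article does not say that only responders are analysed, and it plans best-case and worst-case analyses for patients lost to follow-up. How those would work for multi-item scores at four visits is not spelled out, but the provision exists.
- *That a single mixed model would by itself cut false positives or settle deaths.* It does neither. Reporting each visit keeps four contrasts, and a model on all available scores implicitly extrapolates quality of life beyond death.

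**Conclusion.** The point holds as one of precision in a secondary outcome. The only method stated for continuous outcomes, applied to quality of life as written, leaves out a pre-randomization baseline and three other visits that the trial already collects. For an assumed correlation of 0.3 to 0.7, baseline adjustment would reduce the variance at one visit by 9% to 49% (25% at 0.5), equivalent to raising 113 per arm to about 124 to 222. The direction follows from standard theory, while the size depends on a correlation that the documents do not give. The figures are for a t-test; no separate figure was worked out for the Mann-Whitney test. The R0 analysis, its margin and its sample size are unaffected. The change is worth making because it is nearly free, not because the stated analysis would be invalid.

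**What to change.** In the SAP, before database lock:

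1. Exempt the EQ-5D-5L, QLQ-C30 and PAN-26 scores from the blanket t-test or Mann-Whitney rule.
2. Analyse each scale with a linear mixed model for repeated measures. Include arm, visit, arm-by-visit, baseline score-by-visit and the two stratification factors in the Randomization section (annual center volume and tumor involvement beyond pancreas and spleen). Use all returned questionnaires.
3. Report adjusted mean differences with 95% confidence intervals.
4. Name one principal scale and time point and treat the rest as supportive, since the model alone does not control multiplicity.
5. State that the model assumes missing at random, and specify separately how scores after death are handled.

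Baseline-adjusted models for log CA 19.9 and log CEA, which are also recorded at baseline and follow-up, are an optional extension.

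The cost is SAP wording and somewhat more programming. No new data, patients or visits are needed. If the SAP already specifies such an analysis, it need only say that it replaces the general rule in the article.
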